### Sample size calculation

2.6.

The participants will be randomly divided into functional training group (control group) and hip-knee-ankle Tuina group (intervention group), the allocation ratio of the two groups is 1:1. Sample size calculation is based on the Y-Balance Test (the primary outcome), the sample size formula for comparison of means between two groups in a randomized controlled trial is used to perform the sample size calculation. With the test levels set at *α* = 0.05 (2-sided), *β* = 0.1, according to the relevant literature at home and abroad (31, 35), the maximum acceptable right/left reach distance difference was 4 cm. The standard deviation of the comprehensive score of Y-Balance test in the pre-experimental observation was 4.95. It is substituted into the sample size calculation formula, *n* = 32.15. Considering a 10% dropout rate, and take the integer *n* = 36, so we will include 36 participants for each group, the total number of participants is 72.

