### Data collection and management

2.8.

We will collect the baseline data before the study. The primary and secondary outcomes will be assessed at baseline and 4 weeks (at the end of the intervention). The researcher will collect the data in the case report form (CRF) after obtaining signed consent from the participants. To protect the privacy of the participants, we will use codes and initials instead of their personal information. After data uploading and confirming, only statistician can access to the data.

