### Statistical analysis

2.9.

The principle of Intention-To-Treat (ITT) analysis and Per-Protocol (PP) analysis will be followed in the process of statistical analysis. The Last Observation Carried Forward Analysis (LOCF) rule will be applied for missing data in ITT analysis. All the statistical analysis will be performed using SPSS Ver.25.0 with a significance level of 0.05.

First, the different baseline characteristics of the two groups will be described, data will be presented as mean or median with standard deviation or interquartile range for continuous variables and as frequency distributions for categorical variables. Moreover, the histograms, boxes and other representations will also be considered for the graphic analysis of corresponding data. Two-sample *t*-test for quantitative data or Chi-square test for qualitative data will be performed as homogeneity test, and the covariance analysis will also be performed if an adjustment is needed for a baseline characteristic.

Second, the analyses will focus on whether statistically better treatment outcomes could be achieved in the intervention group. *p* Values less than 0.05 were considered statistically significant and tests were 2-sided.

Third, safety analysis will be performed using the Chi-square test or Fisher's exact test based on the frequency and percentage of all recorded adverse events between two groups.

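### Baseline adjustment depends on observed imbalance; ANCOVA on each outcome's own baseline score should be fixed in advance and always fitted

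*Protocol article*

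**What the plan says.** Protocol section 2.9 (Statistical analysis) first describes the arms at baseline and then compares them by significance test: a two-sample t-test for quantitative variables, while a "Chi-square test for qualitative data will be performed as homogeneity test". The same sentence goes on to say that "the covariance analysis will also be performed if an adjustment is needed for a baseline characteristic". It gives no definition of when adjustment is needed, no threshold and no covariate. The next paragraph, on efficacy, names no model and does not say whether week-4 scores or changes are compared.

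Section 2.8 (Data collection and management) states: "The primary and secondary outcomes will be assessed at baseline and 4 weeks". Each of YBT, CAIT, FAAM and ROM therefore has a baseline value of its own.

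Section 2.6 sizes the trial with the formula for an unadjusted comparison of two means.

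**The concern.** There are three problems with making adjustment conditional.

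- **The test answers the wrong question.** Allocation is random, so any baseline difference is due to chance and its p-value tests a null hypothesis already known to be true. Whether a covariate is worth adjusting for depends on how strongly it predicts the outcome, which the test does not address. With 36 per arm, a non-significant result also leaves room for an imbalance large enough to matter.
- **The model depends on the data.** The decision to adjust comes after the baseline comparison has been seen. An adjusted and an unadjusted result may then both exist, and nothing says which is primary.
- **Precision is given up.** A baseline measurement of the same outcome is usually its best single predictor. When the conditional rule leads to an unadjusted comparison of week-4 scores, that information goes unused.

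At stake are the width of the confidence interval, the chance imbalance left in the estimate, and the reader's confidence that the analysis was fixed beforehand.

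**Working it through.** **Inputs**

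| Input | Value | Source |
|---|---|---|
| Alpha | 0.05, two-sided | Section 2.6 |
| Beta | 0.1 | Section 2.6 |
| Difference | 4 | Section 2.6: "the maximum acceptable right/left reach distance difference was 4 cm" |
| SD | 4.95 | Section 2.6: "The standard deviation of the comprehensive score of Y-Balance test in the pre-experimental observation was 4.95" |
| Dropout | 10% | Section 2.6 |
| Baseline-to-week-4 correlation, r | 0.3 to 0.8 | Assumption; not in the protocol |

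The SD is taken as the between-participant SD at a single time point, and as equal at baseline and week 4.

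**1. The protocol's own figure**

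n = 2 × [SD × (z₀.₉₇₅ + z₀.₉₀) / difference]² = 2 × [4.95 × (1.96 + 1.28) / 4]² = 32.15 per arm, as stated. With 10% dropout, 32.15 / 0.9 = 35.7, so 36 per arm and 72 in total. No baseline correlation enters.

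**2. What adjustment gains**

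ANCOVA on the baseline score reduces the residual SD to SD × √(1 − r²). The equivalent sample-size factor is 1/(1 − r²). Power is from the noncentral t distribution with 32 per arm.

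| r | Residual SD | Power, ANCOVA | Sample-size factor |
|---|---|---|---|
| 0 (unadjusted) | 4.95 | 88.9% | 1.00 |
| 0.3 | 4.72 | 91.5% | 1.10 |
| 0.5 | 4.29 | 95.7% | 1.33 |
| 0.6 | 3.96 | 97.8% | 1.56 |
| 0.7 | 3.54 | 99.4% | 1.96 |

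By the normal approximation, the difference detectable with 90% power at 32 per arm is √(2/32) × residual SD × 3.2416. This is 4.01 unadjusted, 3.47 at r = 0.5 and 2.86 at r = 0.7.

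**3. What the conditional rule delivers**

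The rule was simulated with 100,000 trials per setting and 32 completers per arm: ANCOVA if the baseline t-test of the same outcome gives p < 0.05, otherwise an unadjusted t-test of the week-4 score.

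| r | Type I error, conditional rule | Power, conditional rule | Power, ANCOVA always |
|---|---|---|---|
| 0.3 | 4.7% | 89.2% | 91.1% |
| 0.5 | 4.3% | 89.9% | 95.4% |
| 0.7 | 3.5% | 90.6% | 99.2% |
| 0.8 | 3.1% | 90.8% | >99.9% |

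Either fixed analysis, adjusted or unadjusted, had a type I error of about 5%. The rule recovers almost none of the available precision, because it adjusts in only about one trial in twenty.

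**4. Imbalance that passes the test**

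With 36 per arm, the largest non-significant baseline difference is t₀.₉₇₅,₇₀ × √(2/36) = 0.47 SD, or 0.47 × 4.95 = 2.3 points. In an unadjusted week-4 comparison this shifts the estimate by r × 2.3: about 1.2 points at r = 0.5 and 1.6 at r = 0.7. That is 29% to 41% of the design difference of 4.

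**The case against.** - **The trigger is inferred.** The text does not say that a significant homogeneity test is what prompts adjustment, and it can be read as adding a supplementary analysis beside a fixed unadjusted one. That is fair, but no other criterion is given, and on either reading the decision follows a look at the baseline data.
- **A change score would use the baseline.** Section 2.9 does not exclude one. Its SD is SD × √(2 − 2r). With 32 per arm, power would be 94.5% at r = 0.6 and 98.4% at r = 0.7, against 97.8% and 99.4% for ANCOVA, so the gain could be far smaller than the comparison with week-4 scores suggests. At r = 0.5 a change score gains nothing, and at r = 0.3 its SD is 5.86, worse than the week-4 score alone. ANCOVA is better at every correlation checked from 0.3 to 0.7.
- **The power figures rest on weak inputs.** The correlation is assumed. Section 2.6 also pairs a side-to-side reach difference in centimetres with the SD of a composite score that section 2.5.1.1 defines as a percentage. Both points stand as limits on the power figures. The factor 1/(1 − r²) depends on neither the difference nor the SD.
- **All 36 per arm would be analysed under ITT with LOCF.** Unadjusted power is then 92.2%, and ANCOVA gives 97.4% at r = 0.5 and 99.7% at r = 0.7. The gain falls to about 5 to 7.5 percentage points but remains.
- **No false-positive inflation.** This is correct for the rule as simulated, which is conservative. The largest imbalances would be adjusted for, and the blinded analyst limits steering. Free choice among several baseline characteristics was not simulated.
- **The details may be in an unseen SAP.** A SAP could supply a missing model, but here it would have to reverse a rule that the protocol states.

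**Conclusion.** The concern holds. Section 2.9 makes baseline adjustment conditional on what the baseline data show, although section 2.8 guarantees a baseline value for every outcome. Always fitting ANCOVA would raise power from 88.9% to between 95.7% and 99.4% for assumed correlations of 0.5 to 0.7, or to 91.5% at 0.3, against an unadjusted week-4 comparison with 32 per arm. The conditional rule stays at about 89% to 91% and does not hold its nominal 5% level, erring on the conservative side.

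These sizes rest on an assumed correlation and on the difference and SD in section 2.6 taken at face value. The direction does not: for any correlation that is not trivially small, fixed adjustment is more precise. The flaw is lost efficiency and loose pre-specification. It does not invalidate the trial or its sample size, but it should be corrected.

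**What to change.** State one model for each continuous outcome: ANCOVA of the week-4 score on treatment arm and the baseline value of the same outcome, fitted whatever the observed balance. Apply it to the YBT composite, CAIT, FAAM and ROM, and report the adjusted mean difference with its 95% confidence interval. Name this as the primary analysis; any unadjusted comparison is supportive only.

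Delete the baseline significance tests and the conditional clause, and present baseline characteristics by arm descriptively.

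The cost is a change of wording in the protocol and SAP. No further data or participants are needed, and SPSS 25, already the planned software, fits the model. The change should be made before any outcome data are examined by arm.

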**Discussion:**

The aim of this study is to explore a safe and effective manipulation program and serve as reference for clinical treatment of CAI and expect to provide the necessary theoretical and practical support to our future research.

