In summary, we have designed a randomized controlled clinical trial to explore a safe and effective manipulation program to serve as reference for clinical treatment of ankle injuries. We also expect that this study can help our future research to provide the necessary theoretical and practical support.

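### The only inferential safety analysis stated is a difference test with 36 per arm; a non-significant result would not support the word 'safe', and no interval shows what harm is excluded

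*Protocol article*

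**What the plan says.** Two places bring safety into the aim. The Discussion paragraph of the Abstract says: "The aim of this study is to explore a safe and effective manipulation program and serve as reference for clinical treatment of CAI". The closing paragraph of section 3 (Discussion) says the trial was designed "to explore a safe and effective manipulation program to serve as reference for clinical treatment of ankle injuries".

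Section 2.9 (Statistical analysis) gives the safety analysis in one sentence. It names the method: "safety analysis will be performed using the Chi-square test or Fisher's exact test". The same sentence gives the data that the comparison rests on: "based on the frequency and percentage of all recorded adverse events between two groups". The criterion for tests in that section is: "Values less than 0.05 were considered statistically significant and tests were 2-sided".

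Section 2.6 (Sample size calculation) takes its numbers from the Y-Balance Test only and concludes: "so we will include 36 participants for each group, the total number of participants is 72". The article states no confidence interval, margin or precision target for adverse events. Sections 2.3.3 and 2.3.6 (suspension criteria, patient safety) concern the handling of individual patients and are not an analysis.

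**The concern.** A Chi-square or Fisher test can reject equality of the two arms, but failing to reject does not show that they are alike. In a trial sized for a continuous efficacy measure, a non-significant comparison of adverse events is likely both when there is no excess harm and when there is a moderate one. If the safety result reaches clinicians mainly as a p-value, it says little about how much harm the data rule out. That matters because the result is offered as a reference for treatment.

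A second, smaller difficulty concerns the unit of analysis. The test is based on all recorded adverse events. Each participant has 8 sessions and may have more than one event, whereas a two-by-two test needs one independent observation per participant.

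**Working it through.** **Inputs from the protocol article.** 36 per arm, 1:1, 10% dropout, difference 4, SD 4.95, two-sided alpha 0.05, beta 0.1 (section 2.6); Chi-square or Fisher's exact test, two-sided 0.05 (section 2.9). **Assumed, because the article gives no figure:** the adverse event rates. The background rate is varied from 0% to 10%. Each participant counts once.

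**1. Where the 36 comes from.** n = 2 × [SD × (z₁ + z₂) / difference]² = 2 × [4.95 × (1.96 + 1.28) / 4]² = 32.15 per arm, as stated. Then 32.15 / 0.90 = 35.7, rounded up to 36. The plan's figure is reproduced, and no safety quantity enters it.

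**2. Smallest imbalance that reaches significance, with no control events.** For k versus 0 events, two-sided Fisher p = 2 × C(36, k) / C(72, k).
- k = 5 (13.9% v 0%): 2 × 376,992 / 13,991,544 = 0.054
- k = 6 (16.7% v 0%): 2 × 1,947,792 / 156,238,908 = 0.025

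Fisher's test therefore needs at least 6 v 0. The uncorrected Chi-square test needs 4 v 0 (p = 0.040; 3 v 0 gives p = 0.077).

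**3. Power for a 10-point excess at 36 per arm.** Power is the sum, over all pairs of event counts with p < 0.05, of the product of the two binomial probabilities.

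| Control v Tuina | Fisher | Uncorrected Chi-square |
|---|---|---|
| 0% v 10% | 14.5% | 49.1% |
| 2% v 12% | 14.9% | 41.0% |
| 5% v 15% | 14.6% | 31.7% |
| 10% v 20% | 13.6% | 22.5% |

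The Yates-corrected Chi-square gives the same figures as Fisher. A 10-point excess would be non-significant about 85% of the time under Fisher, and 51% to 78% of the time under the uncorrected Chi-square. With 32 per arm (10% dropout) the ranges are 9% to 11% for Fisher and 20% to 40% for the uncorrected Chi-square.

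**4. Which test would apply.** The expected event cell is half the total number of events. It averages 36 × 0.10 / 2 = 1.8 at 0% v 10%, 36 × 0.20 / 2 = 3.6 at 5% v 15%, and 36 × 0.30 / 2 = 5.4 at 10% v 20%. With the usual threshold of 5, Fisher is the natural choice except near the last scenario, where even the uncorrected Chi-square has only 22.5% power.

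**5. Larger harms.** Fisher power is 46% at 0% v 15%, 75% at 0% v 20%, 92% at 0% v 25%, and 57% at 5% v 25%.

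**6. What an interval would show.** With 0 events in 36 participants, the exact upper limit is 1 − 0.05^(1/36) = 8.0% (one-sided 95%) or 1 − 0.025^(1/36) = 9.7% (two-sided 95%).

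**7. Scale.** 80% power for a 10-point excess needs about 74 per arm at 0% v 10% (93 with continuity correction) and about 141 at 5% v 15% (160 with correction), against 36 planned.

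**The case against.** A reader might infer that the trial will declare Tuina safe because p exceeds 0.05. The article does not say so: section 2.9 names a comparison and no such conclusion. A reader might also take the aim to be delivery of a proven safe program. The wording is only to explore one. The objectives in section 2.1 name stability, balance, ankle function and range of motion; section 2.2 speaks of clinical efficacy; and safety is neither a primary nor a secondary outcome in section 2.5. Nor would the p-value be the only evidence, since section 2.9 names frequencies and percentages, from which the between-arm difference follows.

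It would also go too far to say that the test result hardly depends on whether the treatment is safe. Step 5 shows that a large excess would probably be detected, and the uncorrected Chi-square test is close to even odds at 0% v 10%. All event rates are assumptions. Low power for adverse events is common in trials sized on efficacy, and details such as interval methods are often left to a fuller document.

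These points limit the finding but do not remove it. The article did choose and state an inferential safety method, so the issue is the method stated and not an omitted detail. For moderate harm, that method is non-significant more often than not under either named test, across the whole assumed range. The word 'safe' appears in both summary statements of the aim with nothing in the stated analysis that bounds the harm.

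**Conclusion.** The point holds in a limited form. At 36 per arm, and assuming a 10-point excess over a background of 0% to 10%, the stated safety test has about 14% to 15% power (Fisher) or 22% to 49% (uncorrected Chi-square). A non-significant result would not support calling the program safe. The planned frequencies and percentages help, but without intervals they do not show which harms are excluded. The documents do not support the stronger statement that the plan treats non-significance as proof of safety. Severity is minor: the primary efficacy analysis is unaffected, and the remedy concerns estimation and wording.

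**What to change.** In section 2.9, make the main safety result the number and proportion of participants (not events) in each arm with any adverse event and with any serious adverse event, each with an exact (Clopper-Pearson) 95% confidence interval, plus the between-arm difference with a 95% confidence interval. Keep the Chi-square or Fisher test as supportive only, and state that a non-significant result is not evidence of safety.

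In the Abstract's Discussion paragraph and the closing paragraph of section 3, limit the safety wording to describing adverse events. Note there that even zero events in 36 participants would be compatible with a true rate of up to about 8.0% (one-sided 95%) or 9.7% (two-sided 95%).

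The cost is a few lines of text and one extra table from adverse event data already to be recorded, with no additional participants. The drawback for the sponsor is a less favourable safety statement.

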### Flow chart

2.10.

The Flow chart is detailed in Appendix I below.

## Discussion

3.

Holism is one of the characteristics of traditional Chinese medicine, during the process of diagnosing disease and treatment, how to apply the holistic concept and syndrome differentiation is one of the most important problems in clinical treatment. In the treatment of CAI, Tuina therapy is one of the common and effective treatment methods, and it can also combine the treatment of hip-knee-ankle in a good way, so we have designed a clinical trial for the application of Tuina in the treatment of chronic ankle instability. The aim of this study is to investigate the effects of Tuina based on the concept of hip-knee-ankle conjugation in patients with chronic ankle instability. The stability and balance of lower limbs will be assessed by Y-Balance Test and CAIT scores. The ankle function will be assessed by FAAM scores and ankle range of motion test. The study will attempt to explore the effect of hip-knee-ankle treatment on chronic ankle instability and provide evidence of the effects of Tuina in patients with CAI.

Decreased balance and impaired precise joint movement control are the main consequences of CAI, and recurrent ankle sprain is one of the important causes of this disease. These symptoms ultimately degrade the quality of life and athletic ability of patients with CAI. Although there are previous studies on hip-knee-ankle conjugate theory, they are most applied in the treatment of knee osteoarthritis. This study focus on the effect of hip-knee-ankle conjugate theory on the treatment of CAI, in order to explore how to improve the stability and balance of lower limbs and ankle function by using manipulation and improve the quality of life and motor ability of the patients with CAI.

Although the aim of this trial is to explore the effect of Tuina on ankle injuries and address the limitations of previous studies, this study also has its own limitations. First, because it is impossible to blind the doctor and participants, it is difficult to design a double-blinded RCT. To minimize the risk of detection bias, we have a randomization specialist, he will divide the participants into two groups randomly prior to the study, the assessors and analyst will be blinded to the group assignment in this study. Second, due to lack of precision instruments, lower limb stability, balance ability and ankle range of motion can only be assessed manually, which inevitably leads to certain errors.

In summary, we have designed a randomized controlled clinical trial to explore a safe and effective manipulation program to serve as reference for clinical treatment of ankle injuries. We also expect that this study can help our future research to provide the necessary theoretical and practical support.

## Trial status

4.

The version number of this protocol is 2.0, dated on 10 January 2023. Participants will be recruited between March 2023 and June 2024. Study completion is expected to be October 2024.

## Ethics statement

The studies involving human participants were reviewed and approved by IRB of Shuguang Hospital afiliated with Shanghai University of Traditional Chinese Medicine (Approved number of ethic committee: 2022-1226-163-01). The patients/participants provided their written informed consent to participate in this study.
